#### **4.9. Contraindications to subsequent vaccination**

##### **4.9.1. Indications for deferral of vaccination**

The following AEs constitute contraindications to administration of RTS,S/AS02D or RTS,S/AS01E at that point in time; if any one of these AEs occur at the time scheduled for vaccination, the subject may be vaccinated at a later date, within the time window specified in the protocol, or withdrawn at the discretion of the investigator. AEs should be followed-up according to the instructions in Section 8.6:

- Acute disease at the time of administration of investigational product (acute disease is defined as the presence of a moderate or severe illness with or without fever). All vaccines can be administered to persons with a minor illness such as diarrhea or mild upper respiratory infection without fever, i.e. axillary temperature  $< 37.5^{\circ}\text{C}$ .
- Axillary temperature of  $\geq 37.5^{\circ}\text{C}$ .

##### **4.9.2. Absolute contraindications to further vaccination**

The following AEs constitute absolute contraindications to further administration of RTS,S/AS02D or RTS,S/AS01E; if any of these AEs occur during the study, the subject must not receive additional doses of vaccine, but may continue other study procedures at the discretion of the investigator. AEs should be followed-up according to the instructions in Section 8.6:

- Acute allergic reaction (significant IgE-mediated events) or anaphylaxis following the administration of vaccine investigational product.
- Any confirmed or suspected immunosuppressive or immunodeficient condition, including human immunodeficiency virus (HIV) infection.
- Failure to thrive.

## **5. CONDUCT OF STUDY**

### **5.1. Ethics and regulatory considerations**

The study will be conducted according to Good Clinical Practice (GCP), the Declaration of Helsinki (Protocol Appendix A), and local rules and regulations of the country.

Submission of the protocol and any protocol amendments to regulatory agencies will occur in accordance with local regulatory requirements. The timing of the submission relative to IEC/IRB submission or approval and whether or not the authority will provide their approval of or favorable opinion on the protocol or amendment before it can be implemented will depend on local regulatory requirements.

#### **5.1.1. Institutional Review Board/Independent Ethics Committee (IRB/IEC)**

Each IRB/IEC will be constituted according to the local laws/customs of each participating country. The ICH Harmonized Tripartite Guideline for Good Clinical Practice recommends that IRBs/IECs should include:

- a. At least five members.
- b. At least one member whose primary area of interest is in a non-scientific area.
- c. At least one member who is independent of the institution/ study site.

Only those IRB/IEC members who are independent of the investigator and the sponsor of the study will vote/ provide opinion on a study-related matter.

A list of the professions of the IRBs'/IECs' members will be obtained by the PI or delegate.

This protocol and any other documents that the IRBs/IECs may need to fulfill their responsibilities, including subject recruitment procedures and information about payments and compensation available to subjects, will be submitted to each IRB/IEC by the PI or delegate. Written and dated unconditional approval/favorable opinion from each IRB/IEC of the protocol and amendment (if any and applicable), written informed consent form (ICF), consent form updates (if any), subject recruitment procedure(s) (e.g. advertisements), and any other written information to be provided to subjects will be in the possession of the investigator and GSK before commencement of the study. This approval/favorable opinion will refer to the study by study title and number with exact protocol version and date, and will identify the documents reviewed and state the date of review. Relevant GSK Biologicals' data will be supplied by the GSK Biologicals' Central Study Coordinator to the independent IRBs/IECs for review and approval of the protocol. Verification of IRBs/IECs unconditional approval of the protocol and the written informed consent statement will be transmitted by the PI to the GSK Biologicals' Central Study Coordinator, using the standard notification form, prior to shipment of vaccine supplies and CRFs to the site.

No deviations from, or changes to, the protocol will be initiated without prior written sponsor and IRBs'/IECs' approval/ favorable opinion of an appropriate amendment, except when necessary to eliminate immediate hazards to the subjects or where permitted by all applicable regulatory requirements or when the change(s) involves only logistical or administrative aspects of the study (e.g., change of monitor[s], telephone number[s].) Administrative changes and amendments not submitted for approval will be submitted to the IRB/IEC for information only. However, written verification that such documents were submitted will be obtained. Approvals/ verifications will be transmitted in writing by the PI.

The IRB/IEC will be informed by the GSK Biologicals' Central Study Coordinator of:

- all subsequent protocol amendments, informed consent changes or revisions of other documents originally submitted for review,
- serious and/or unexpected adverse events occurring during the study,
- all subsequent protocol administrative changes (for information),
- new information that may affect adversely the safety of the subjects or the conduct of the study,
- regular updates and/or request for re-approval,
- when the study has been completed.

If the trial is prematurely terminated or suspended for reasons including, but not limited to, safety or ethical issues or severe non-compliance, the sponsor will promptly inform the regulatory authorities of the termination or suspension and the reason(s) for the termination or suspension. If required by applicable regulations, the investigator will inform the IEC/IRB promptly and provide the reason for the suspension or termination (see Appendix B for further details).

### **5.1.2. Informed consent**

The details of the informed consent process are provided in Appendix C. The following principles will also apply.

In obtaining and documenting informed consent, the investigator will comply with the applicable regulatory requirement(s), and will adhere to GCP and to the ethical principles that have their origin in the appended Declaration of Helsinki. Prior to the beginning of the trial, the investigator will have the IRBs'/IECs' written approval/favorable opinion of the written informed consent form and any other written information to be provided to the subjects' parents/guardians.

Information will be given in both oral and written form whenever possible and as deemed appropriate by the IRBs/IECs.

An investigator or designate will describe the protocol to potential subjects' parents/guardians face to face. The ICF may be read to the subjects' parents/guardians, but, in any event, the investigator or designate shall give the subjects' parents/guardians

ample opportunity to inquire about details of the study and ask any questions before dating and signing the ICF.

ICFs will be in a language fully comprehensible to the prospective subjects' parents/guardians. Informed consent shall be documented by the use of a written ICF approved by the IRBs/IECs and signed/thumbprinted and dated by the subjects' parents/guardians and by the person who conducted the informed consent discussion. The parent(s)/guardian(s) signature/thumbprint confirms the consent is based on information that has been understood. All individuals will have the study and the ICF explained to them point by point by the interviewer. Where parent(s)/guardian(s) are illiterate, an impartial witness will be present. The subjects' parents/guardians will sign (or thumbprint, where illiterate) the consent form. When parent(s)/guardian(s) are illiterate, the witness will also sign and date the consent form.

Each subject's signed informed consent form will be kept on file by the investigator for possible inspection by Regulatory Authorities and/or GSK Biologicals' Professional and Regulatory Compliance persons. The subjects parent(s)/guardian(s) will receive a copy of the signed and dated written informed consent form and any other written information provided to the parent(s)/guardian(s) and will receive copies of any signed and dated consent form updates. Any amendments to the written information will be provided to subjects parent(s)/guardian(s).

Both the informed consent discussion and the written informed consent form and any other written information to be provided to the subjects' parent(s)/guardian(s) will include explanations of the following:

- a. That the trial involves research.
- b. The purpose of the trial.
- c. The trial vaccine regimens and the probability for random assignment to each vaccination regimen.
- d. The trial procedures to be followed, including all invasive procedures.
- e. The subject's parents'/guardians' responsibilities.
- f. Those aspects of the trial that are experimental.
- g. The reasonably foreseeable risks or inconveniences to the subjects.
- h. The reasonable expected benefits.
- i. The alternative procedure(s) or course(s) of treatment/ methods of prevention that are available to subjects, and their important potential benefits and risks.
- j. The compensation and/or treatment available to subjects in the event of trial-related injury.
- k. The anticipated expenses to subjects' parents/guardians for participating in the trial.
- l. That the subjects' participation in the trial is voluntary and subjects' parents/guardians may refuse to participate or withdraw from the trial, at any time, without penalty or loss of benefits to which subjects are otherwise entitled.

- m. That the monitor(s), the auditor(s), the IRBs/IECs, and the regulatory authority(ies) will be granted direct access to the subject's original medical records for verification of clinical trial procedures and/or data, without violating the confidentiality of subjects, to the extent permitted by the applicable laws and regulations and that, by signing a written informed consent, the subject's parents/guardians are authorizing such access.
- n. That records identifying subjects will be kept confidential and, to the extent permitted by the applicable laws and/or regulations, will not be made publicly available. If the results of the trial are published, subjects' identity will remain confidential.
- o. That the subjects' parents/guardians will be informed in a timely manner if information becomes available that may be relevant to the subjects' parents/guardians willingness for continued participation in the trial.
- p. The person(s) to contact for further information regarding the trial and the rights of trial subjects, and who to contact in the event of trial-related injury.
- q. The foreseeable circumstances and/or reasons under which a subject's participation in the trial may be terminated.
- r. The expected duration of a subject's participation in the trial.
- s. The approximate number of subjects involved in the trial.

GSK Biologicals will prepare a model ICF which will embody all the elements described above. While it is strongly recommended that this model document be followed as closely as possible, the informed consent requirements given in this document are not intended to pre-empt any local regulations which require additional information to be disclosed for informed consent to be legally effective. Clinical judgment, local regulations and requirements will guide the final structure and content of the document.

The investigator has the final responsibility for the final presentation of ICF, respecting the mandatory requirements of local regulations. The ICF generated by the investigator with the assistance of the sponsor's representative, will be approved (along with the protocol, and any other necessary documentation) by the IRBs/IECs and be acceptable to GSK Biologicals.

### **5.1.3. Safety monitoring plan**

This trial is overseen by a Data Safety Monitoring Board (DSMB), operating under a charter, assisted by a Local Safety Monitor (LSM).

The DSMB will be notified of all SAEs within 24 hours. In addition there are defined points during the trial at which cumulative safety data will be reviewed by the LSM and the DSMB. There will be two reports as defined in Section 5.1.3.3.

The PI, LSM and DSMB are empowered to suspend the trial for any safety concern. To supplement this, the protocol defines criteria for the suspension of vaccination (refer to Section 5.1.3.4).

**5.1.3.1. Data Safety Monitoring Board (DSMB)**

An independent committee consisting of experts in malaria, pediatrics, statistics and other appropriate disciplines has been appointed to oversee ethical and safety aspects of the study conduct. A quorum of 3 members is required at scheduled meetings.

The role of the DSMB includes the review of the implementation and progress of the study. It provides initial, regular, and closing advice on safety-related issues to GSK Biologicals. Its advice is based on the interpretation of study data with reference to the study protocol.

The DSMB will confer before the initiation of the study (pre-initiation review), during the study at points of safety review and at the close of the study. They will review the Protocol and Report and Analysis Plan (RAP). Other unscheduled meetings may be required. Meetings must be documented and minutes made available to the sponsors. The DSMB may, if deemed necessary, convene a meeting with, or request further information from the Principal Investigators, the Medical Monitor/Local Safety Monitor and GSK Biologicals' and MVI at PATH's designated project representatives at any stage of the study.

The DSMB is empowered to suspend the enrollment to the trial and/or vaccination on the trial pending review of potential safety issues; complete details of this process are given in Section 5.1.3.4.

**5.1.3.1.1. Data Reviewed by the DSMB**

The DSMB must be informed by the Local Safety Monitor (LSM) of the following safety data on an 'as received' basis:

- All SAEs;
- All withdrawals of study subjects by the Principal Investigator or the parent(s)/guardian(s) of a subject due to adverse events.

The DSMB will receive from the sponsor, GSK Biologicals:

- Safety summary reports at two predefined timepoints as defined in Section 5.1.3.3;
- New information that may affect adversely the safety of the subjects or the conduct of the study;
- All subsequent protocol amendments, ICF changes or revisions of other documents originally submitted for review;
- All subsequent protocol modifications (for information).

**5.1.3.2. Local Safety Monitor (LSM)**

The overall role of the Local Safety Monitor (LSM), who is an experienced clinician based in Lambaréné, will be to support the clinical investigators and to act as a link between the investigators and the DSMB.

The LSM's role will include:

- Acting as the study volunteer's advocate;
- Promptly communicating relevant safety information to the DSMB;
- Providing advice to the investigators on whether a set of clinical circumstances in a study warrants formal notification to the DSMB;
- Unblinding a subject if deemed necessary to allow for adequate treatment;
- Liaising closely with the chair of the DSMB throughout the course of the trial;
- Suspension of vaccination for a major safety concern pending discussion with the DSMB (see Section 5.1.3.4 for full details).

#### **5.1.3.2.1. Data Reviewed by the LSM**

The LSM must be informed by the investigator on an 'as received' basis of:

- All SAEs;
- All withdrawals of study subjects by the Principal Investigator or the parent(s)/guardian(s) of a subject due to adverse events.

#### **5.1.3.3. Safety monitoring reports**

Safety reports will be produced for the DSMB on all data collected until two points in the study; after 40 subjects have been enrolled and have completed the first 7 days of follow-up post Dose 1 and after 40 subjects have completed the first 7 days of follow-up post Dose 2. An independent statistician will analyze the data and prepare an unblinded report for the DSMB thereby maintaining the blind of the malaria project team at GSK Biologicals and the investigator group. If a criterion for the suspension of progression to the next sequential vaccine dose is met, or the DSMB have any safety concerns about the vaccines, they may suspend the progression to the next vaccine dose. The process outlined in Section 5.1.3.4 will be followed.

The reports will contain for the first 40 children to receive each sequential vaccine dose:

- All SAEs and any relationship to vaccine (RTS,S/AS02D or RTS,S/AS01E) to date;
- For each of the first two doses (i.e. after Dose 1 and Dose 2) of RTS,S/AS02D and RTS,S/AS01E, all solicited AEs tabulated by severity grading (any and Grade 3 alone – refer to Table 9) and relationship to vaccine;
  - Should the investigator judge a case of Grade 3 fever to be unrelated to vaccination, an alternative explanation for the cause of the fever will be provided
- For each of the first two doses (i.e. after Dose 1 and Dose 2) of RTS,S/AS02D and RTS,S/AS01E, all unsolicited AEs tabulated by severity grading (any and Grade 3 alone – refer to Table 9) and relationship to vaccine;

- All laboratory values up to 30 days post Dose 2 presented as number of subjects out of range (above and below normal range) at each sampling time point (post doses 1 and 2 of RTS,S/AS02D or RTS,S/AS01E) tabulated by toxicity grading scale (refer to Table 10);
  - For all subjects with toxicity grading scale  $\geq 3$ , full clinical details will be provided
- All withdrawals of study subjects by the Principal Investigator due to adverse events recorded from the children or withdrawals of children by the parent(s)/guardian(s) following doses of RTS,S/AS02D or RTS,S/AS01E (expressed as percentage of subjects enrolled).

#### **5.1.3.4. Process for the suspension of progression to the next sequential vaccine dose**

Suspension of the next sequential vaccine dose, pending full review of available data by the DSMB will take place if:

- The Principal Investigator suspends vaccination for any of the following SAEs pending review by the DSMB;
  - Death or life-threatening SAE which is judged to be related to the study vaccine;
  - Anaphylactic shock reaction in an enrolled subject following vaccination.
- The DSMB recommend suspension of all vaccination for any one SAE or pattern of SAEs. The DSMB will communicate their recommendation to the Principal Investigator who will enact it. The DSMB will notify the sponsors of their decision immediately;
- A safety report shows  $> 5\%$  of subjects vaccinated with RTS,S/AS01E, or  $> 5\%$  of subjects vaccinated with RTS,S/AS02D are withdrawn by the investigator for local or systemic reactogenicity in recipients;
  - In making their recommendation the DSMB will take into account the full clinical history of each withdrawn child.
- A safety report shows  $> 5\%$  of doses of RTS,S/AS02D or  $> 5\%$  of doses of RTS,S/AS01E are followed by fever  $> 39.0^{\circ}\text{C}$  judged to be related to vaccination in recipients of RTS,S/AS01E;
  - In making their recommendation the DSMB will review the investigators assessment of relatedness of all Grade 3 fevers (refer to Table 9).
- The DSMB recommend suspension of enrollment following their review of a safety summary reports.

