#### **5.1.3.5. Process if the trial is suspended on the basis of safety reports on first 40 subjects to receive each of the first two vaccine doses**

If the trial is suspended, the DSMB will review all available information (which will include the experience of all children to have been vaccinated) and make a recommendation to the study sponsor (GSK Biologicals) whether to recommence the trial

and proceed to the next sequential vaccine dose, or to stop the trial permanently. In the event that the DSMB recommend to stop the trial permanently, the FDA will be informed by GSK Biologicals that the trial is suspended.

Although the trial may be suspended by the DSMB, the LSM or the Principal Investigator, it is the responsibility of the sponsor (GSK Biologicals) to make the recommendation whether or not the trial should be stopped permanently.

In the event that the trial is suspended on the recommendation of the DSMB the sponsor (GSK Biologicals) will evaluate the information. If the sponsor concurs with the DSMB's recommendation to suspend the trial, GSK Biologicals will inform the FDA that the trial has been stopped permanently. If the sponsor's recommendation is to continue, then a report will be submitted to the FDA detailing the rationale used in reaching this decision. The agreement of the FDA will be obtained prior to restarting the trial.

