#### **5.4. Vaccination process**

The vaccines RTS,S/AS02D and RTS,S/AS01E will be packaged in identical boxes and will be identified by a treatment number. The unique treatment number will identify all doses of these vaccines administered to each subject. After randomization the treatment number assigns the subject to one group or another in a blinded way. Each subject will retain the same treatment number for their subsequent vaccine doses. The treatment number will be recorded on the subject's Clinic Form after the vaccine has been administered; information from the Clinic Form is subsequently transferred to the Case Report Form. The Clinic Form and Case Report Form link the subject number and the treatment number.

All vaccines will be administered by the intramuscular route to the left deltoid. Subjects who receive their vaccination in the incorrect arm will continue to receive subsequent blinded vaccinations as normal. The fact that the vaccine was administered in the wrong arm will be documented.

Vaccinations will take place at the HAS MRU or the outpatient clinic of HAS. All vaccinations will be given by a qualified person; a nurse or a doctor. A staff member experienced in the resuscitation of children will be available at all vaccination sessions. Facilities and equipment will be available to give emergency treatment in the case of an anaphylactic reaction following administration of vaccines. All children will be observed for an hour after the administration of vaccine to evaluate and treat any acute adverse events.

The process for each vaccination is as follows. The identity of the child will be confirmed using the study identification card. The subject number on this card will be cross-checked with that on the subject's clinic form, ensuring that the subject number on the clinic form matches that of the study identification card. On the day of the first vaccination the contraindications to vaccination, inclusion/exclusion criteria and ICF will be checked prior to vaccination. On the days of the subsequent vaccinations, elimination criteria and

contraindications to vaccination will be checked prior to vaccination. A vaccine clinic form will be initiated, which will give the child's identifiers, subject number and treatment number assigned after the administration of the vaccine.

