## **5.6. Monitoring of hematological and biochemical laboratory parameters**

Blood for safety monitoring of hematology, renal and hepatic function will be measured at screening, one week post Dose 1, one month post Dose 3 and 12 months post Dose 3. The hematological and biochemical parameters will be documented on the CRF. For all values outside the normal range (refer to Table 10), the reason and/or clinical condition will be documented. Results of hematological and biochemical laboratory tests will be reviewed as soon as they are generated. Any value outside the normal range will be managed as appropriate by a medically qualified individual under the supervision of the Principal Investigator (refer to Section 8.6). Guidance on when to report abnormalities as SAEs is given in Section 8.3.

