**Clinic Visit 3: Post Dose 1 follow-up visit in Clinic**  
Day 6

---

- Check study identification card of vaccinee
- Carry out physical examination
- Record axillary temperature of subject
- Record local (pain and swelling at the injection site) and general (fever, irritability / fussiness, drowsiness, loss of appetite) solicited adverse events
- Record SAEs experienced by the vaccinee since the last visit
- Record unsolicited adverse events experienced by the vaccinee since the last visit
- Check elimination criteria
- Record concomitant medication
- Blood sample to collect a minimum 1 mL blood for analysis of:
  - hematology (complete blood count)
  - biochemistry (creatinine, ALT and bilirubin)

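### The fever suspension criterion sets a threshold for both vaccines but ends with a phrase confined to RTS,S/AS01E recipients, so its RTS,S/AS02D limb is empty on one reading and the rule is ambiguous at best

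*Protocol*

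**What the plan says.** Protocol section 5.1.3.4 lists the conditions under which the next sequential dose is suspended pending DSMB review. Two of them are numerical.

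- **Withdrawals.** The criterion is met if more than 5% of the subjects given either vaccine are withdrawn by the investigator for reactogenicity. Each vaccine is named with its own threshold, and the closing words single out neither.
- **Fever.** The criterion names more than 5% of RTS,S/AS02D doses or more than 5% of RTS,S/AS01E doses followed by fever above 39.0°C. It ends "judged to be related to vaccination in recipients of RTS,S/AS01E". Its sub-bullet has the DSMB review the relatedness assessment of all Grade 3 fevers, without limiting this to one vaccine.

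Two other sections bear on how the closing phrase is read. Section 5.4 states: "Each subject will retain the same treatment number for their subsequent vaccine doses". Section 5.1.3.3 requires the DSMB reports to show, by grade and relatedness, "For each of the first two doses (i.e. after Dose 1 and Dose 2) of RTS,S/AS02D and RTS,S/AS01E, all solicited AEs tabulated".

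**The concern.** The two limbs of the fever criterion share one predicate, and the natural grammatical reading applies the closing phrase to both. A child keeps one treatment number, and so one vaccine, for all three doses. Under planned dosing, therefore, no RTS,S/AS02D dose is followed by a fever in an RTS,S/AS01E recipient. On that reading the RTS,S/AS02D threshold is written into the rule but nothing can count towards it, and no other section corrects this.

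The rule can hold dosing in children aged 18 months to 4 years, and the Glossary classes both vaccines as investigational products. Whether it is met for one of the two arms should not depend on how the statistician preparing the report, or a DSMB member, parses its last phrase.

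**Working it through.** The protocol gives the 5% threshold but no operating characteristic for it, so there is no stated figure to reproduce. The check is first textual, then a small illustration.

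**Text, side by side**

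1. The fever criterion gives RTS,S/AS02D its own threshold. That would be pointless if only fevers in RTS,S/AS01E recipients counted.
2. The parallel withdrawal criterion, directly above it, covers both vaccines and has no such restriction at its end.
3. The fever sub-bullet sends all Grade 3 fevers to the DSMB for review of relatedness.
4. Section 5.1.3.3 tabulates solicited events for both vaccines in an unblinded report.
5. Section 5.4 rules out planned crossover between vaccines.

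Items 1 to 4 establish the intent, which is both vaccines. Item 5 shows that the closing phrase defeats that intent for RTS,S/AS02D if it governs both limbs.

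**Illustration of what the RTS,S/AS02D limb would do**

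Inputs: reports on 40 children (section 5.1.3.3) and 1:1 randomization (section 3). Assumptions: an even split giving 20 doses per arm, independent events, and true related-fever rates p chosen for illustration.

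More than 5% of 20 means more than 1, so the limb is met at 2 or more fevers (2/20 = 10%). The probability is

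P(X ≥ 2) = 1 − (1 − p)^20 − 20p(1 − p)^19.

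- p = 5%: 1 − 0.3585 − 0.3774 = 0.26
- p = 10%: 1 − 0.1216 − 0.2702 = 0.61
- p = 20%: 1 − 0.0115 − 0.0576 = 0.93

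On the literal reading the probability is 0 at every p, because no event is eligible.

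The result moves with the number of doses per arm:

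| RTS,S/AS02D doses | Fevers needed for more than 5% | p = 5% | p = 10% | p = 20% |
|---|---|---|---|---|
| 18 | 1 (5.6%) | 0.60 | 0.85 | 0.98 |
| 20 | 2 (10.0%) | 0.26 | 0.61 | 0.93 |
| 22 | 2 (9.1%) | 0.30 | 0.66 | 0.95 |
| 40 | 3 (7.5%) | 0.32 | 0.78 | 0.99 |

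The 40-dose row corresponds to pooling both doses at the second report, which the text leaves open. In every row the literal reading gives 0.

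**The case against.** The strongest reply is that this is a drafting slip that most readers would resolve correctly. The closing phrase can be attached to the nearer RTS,S/AS01E limb only. It is then redundant, and the RTS,S/AS02D limb works. The context listed above points the same way. This stands: the criterion is ambiguous rather than certainly void, and the intent is not in doubt. It does not make the wording sound, because the reading that saves the rule leaves the phrase with no function.

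The second reply is that dosing would not go ahead unreviewed. Under the Synopsis the DSMB authorizes progression after seeing the first 40 children. Under section 5.1.3.3 it receives both arms unblinded and may suspend for any concern about the vaccines. Section 5.1.3 gives the investigator and the Local Safety Monitor similar power. The limb for the new formulation, RTS,S/AS01E, is intact on either reading. All of this stands and bounds the harm, but discretion does not repair the pre-specified rule.

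The third reply is that the probabilities are hypothetical. That is so. The protocol gives no related-fever rates for children, and section 1.5 describes only comparable reactogenicity of the adult formulations. The figures describe a limb of the rule, not the chance of a different DSMB decision.

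**Conclusion.** The closing phrase is wrong as written. If it governs both limbs, the RTS,S/AS02D fever threshold cannot be met under planned dosing. If it governs only one, it is superfluous and the criterion is ambiguous. It is a wording defect in an operative safety rule. Practical harm is limited, and no endpoint, analysis or sample size is affected. The illustrative contrast (0.26, 0.61 and 0.93 against 0) rests on the assumed 20 doses per arm, independence and the chosen rates.

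Three stronger inferences are not supported:

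- **That RTS,S/AS02D was deliberately exempted.** Its own threshold in the same sentence and the parallel withdrawal criterion say otherwise.
- **That children given RTS,S/AS02D lack fever oversight.** The DSMB sees their data and authorizes each progression.
- **That the limb could never be met in any circumstance.** The argument is confined to planned dosing. Appendix G allows for a dose being given to another subject by mistake.

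A reader might also infer from the per-dose tabulation in section 5.1.3.3 that the 5% must be counted separately for each sequential dose. Section 5.1.3.4 does not say so. Reports cover all data collected to each point, so pooled counting at the second report is equally open.

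**What to change.** In section 5.1.3.4, end the fever criterion at the word *vaccination* and delete the final restriction to RTS,S/AS01E recipients. Alternatively, replace that restriction with *in recipients of that vaccine*. The rule then applies the existing 5% threshold to related fevers above 39.0°C after doses of either vaccine. It needs no new threshold and no new counting rule.

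If the DSMB charter or the report template repeats the sentence, make the same change there. The cost is one phrase, with no added visits, samples or subjects.
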